## Abstract

**Background:**

In patients requiring general anesthesia, lung-protective ventilation can prevent postoperative pulmonary complications, which are associated with higher morbidity, mortality, and prolonged hospital stay. Application of positive end-expiratory pressure (PEEP) is one component of lung-protective ventilation. The correct strategy for setting adequate PEEP, however, remains controversial. PEEP settings that lead to a lower pressure difference between end-inspiratory plateau pressure and end-expiratory pressure (“driving pressure,” ΔP) may reduce the risk of postoperative pulmonary complications. Preliminary data suggests that the PEEP required to prevent both end-inspiratory overdistension and end-expiratory alveolar collapse, thereby reducing ΔP, correlates positively with the body mass index (BMI) of patients, with PEEP values corresponding to approximately 1/3 of patient’s respective BMI. Thus, we hypothesize that adjusting PEEP according to patient BMI reduces ΔP and may result in less postoperative pulmonary complications.

**Methods:**

Patients undergoing general anesthesia and endotracheal intubation with volume-controlled ventilation with a tidal volume of 7 ml per kg predicted body weight will be randomized and assigned to either an intervention group with PEEP adjusted according to BMI or a control group with a standardized PEEP of 5 mbar. Pre- and postoperatively, lung ultrasound will be performed to determine the lung aeration score, and hemodynamic and respiratory vital signs will be recorded for subsequent evaluation. The primary outcome is the difference in ΔP as a surrogate parameter for lung-protective ventilation. Secondary outcomes include change in lung aeration score, intraoperative occurrence of hemodynamic and respiratory events, oxygen requirements and postoperative pulmonary complications.

**Discussion:**

The study results will show whether an intraoperative ventilation strategy with PEEP adjustment based on BMI has the potential of reducing the risk for postoperative pulmonary complications as an easy-to-implement intervention that does not require lengthy ventilator maneuvers nor additional equipment.

**Trial registration:**

German Clinical Trials Register (DRKS), DRKS00031336. Registered 21st February 2023.

**Trial status:**

The study protocol was approved by the ethics committee of the Christian-Albrechts-Universität Kiel, Germany, on 1st February 2023. Recruitment began in March 2023 and is expected to end in September 2023.

## Introduction

### Background and rationale {6a}

An increasing number of patients suffer from, partly undiagnosed, pulmonary diseases and other risk factors such as obesity, that pose major challenges to mechanical ventilation. Approximately 5% of patients undergoing surgery under general anesthesia and thus mechanical ventilation develop postoperative pulmonary complications (PPCs). These are associated with higher morbidity and mortality and prolonged hospital stay [1].

Lung-protective ventilation during general anesthesia can help to prevent these PPCs and improve outcomes [2]. Components of lung-protective ventilation include low tidal volumes and adequate positive end-expiratory pressure (PEEP). However, the proper strategy for setting PEEP during general anesthesia is still controversial. Randomized controlled trials comparing higher vs. lower PEEP settings without individualization found no difference in PPCs between higher and lower PEEP [3, 4]. Some evidence suggests that changes in ventilatory settings that result in a reduction in the pressure difference between end-inspiratory plateau pressure and end-expiratory pressure (“driving pressure,” ΔP) may help reduce the risk for PPCs [5]. Previously published approaches for intraoperative individualization of PEEP and reduction of ΔP include adjustment of PEEP according to transpulmonary pressure [6, 7] and performing a decremental PEEP trial and subsequently selecting PEEP according to best respiratory system compliance [7, 8] or with electrical impedance tomography [9, 10]. These methods of individualizing PEEP, however, are not without risk to the patient, are time consuming, and are not easy to implement in routine anesthesiology practice. We therefore sought to develop a method for individual PEEP adjustment that requires neither time-consuming ventilatory maneuvers nor additional equipment.

In a previous study, we found that the PEEP level needed to minimize both end-inspiratory overdistension and alveolar collapse during mechanical ventilation for general anesthesia in flat supine position was positively correlated with the patient’s body mass index and can be estimated using the regression equation PEEP = BMI/3 [11]. In a group of 25 obese patients with an average BMI of 48.3 (BMI/3 = 16.1), Nestler et al. found that the PEEP level required to minimize the regional ventilation delay index (an EIT measure that correlates with tidal recruitment) was 18.5 ± 4.6 mbar and was positively correlated with BMI [9]. In another EIT study investigating the PEEP level required to minimize both end-inspiratory overdistension and alveolar collapse during mechanical ventilation for general anesthesia that included 40 patients (average BMI: 29.5 $$\to$$ BMI/3 = 9.8), Pereira et al. found an average required PEEP level of 10.3 ml/mbar in the open abdominal surgery group that was also positively correlated with patient’s BMI [10]. In 37 patients scheduled for elective bariatric surgery with an average BMI of 48.3 kg/m^2^ (BMI/3 = 16.1), Eichler et al. found that the target of a positive transpulmonary pressure at end expiration was achieved at PEEP levels of 16.7 cmH_2_O [6].

In summary, these studies suggest that the PEEP needed to prevent both end-inspiratory overdistension of the lung and end-expiratory alveolar collapse during general anesthesia, thereby reducing the ΔP, is positively correlated with the patient’s BMI, with required PEEP levels corresponding on average to approximately one-third of the patient’s respective BMI. We therefore hypothesize that adjusting PEEP to a level corresponding to one-third of the patient’s BMI could lead to a reduction of ΔP and may thus help to prevent PPCs.

### Objectives {7}

The main objective of this study is to evaluate the efficacy of a BMI-adjusted PEEP compared with a standardized PEEP of 5 mbar in reducing the pressure difference between end-inspiratory plateau pressure and end-expiratory pressure. Secondary objectives will examine the difference between intervention and control group concerning respiratory system mechanics, hemodynamics, need for rescue maneuvers, and changes in ultrasound lung aeration score.

### Trial design {8}

The BodyVent trial is a randomized, controlled, patient blinded single-center superiority trial with two parallel groups and a primary endpoint of driving pressure (ΔP) within volume-controlled ventilation in endotracheally intubated patients during general anesthesia. Randomization is performed by random permuted block randomization with a 1:1 allocation ratio.

## Methods: participants, interventions, and outcomes

### Study setting {9}

The study will be performed within the University Medical Center Schleswig–Holstein, Germany’s third-largest university hospital with annually more than 110,000 inpatients. The trial will include patients who will undergo a planned surgery under general anesthesia with endotracheal intubation in the central operating room at Campus Kiel.

### Eligibility criteria {10}

To be eligible, patients must meet the following inclusion criteria: [1] Surgery under general anesthesia with endotracheal intubation is planned, [2] the expected duration of surgery exceeds 2 h, [3] participants are at least 18 years of age, and [4] written informed consent is obtained. Potential patients will be excluded if any of the following exclusion criteria are fulfilled: [1] planned intraoperative ventilation via a face mask or a laryngeal mask airway, [2] laparoscopic surgery, thoracic surgery or surgery with cardiopulmonary bypass is planned, [3] surgery will be performed in > 10° Trendelenburg/Anti-Trendelenburg position, [4] pregnancy, [5] BMI > 60, [6] acute cardiac decompensation, [7] severe pre-existing pulmonary conditions (e.g., acute pulmonary decompensation, acute respiratory distress syndrome, pulmonary fibrosis, present pneumonia, chronic obstructive pulmonary disease severity GOLD IV), [8] inability to give informed consent.

### Who will take informed consent? {26a}

At the pre-medication outpatient clinic patients will be screened daily (Monday–Friday) for possible study inclusion. After detailed information about the BodyVent trial is given, patients will be asked to give written informed consent for the collection of demographic and clinical data and overall study participation by a physician member of the research team. In accordance with the Declaration of Helsinki and national regulations, patients have the right to withdraw their consent at any time and without need to specify reasons without compromising their future medical care.

### Additional consent provisions for collection and use of participant data and biological specimens {26b}

Ancillary studies are currently not planned. The existing declaration of consent also covers possible future projects or the transfer of pseudonymized data to scientific cooperation partners.

## Interventions

### Explanation for the choice of comparators {6b}

In normal weight patients, a PEEP setting of 5 mbar is considered as clinical standard. With an increasing number of overweight patients, a weight-adapted PEEP adjustment may be necessary. To be able to clinically apply optimal and standardized ventilation parameters for individual, weight-adjusted ventilation, an easy-to-apply calculation method is needed. Thus, we consider a comparison between a control group with standard therapy (PEEP 5 mbar) and an intervention group (PEEP BMI/3 mbar) to be useful. The same inclusion and exclusion criteria will be used to recruit the intervention and control group.

### Intervention description{11a}

Only patients who provide consent will be included in the study. After obtaining written informed consent, total height, weight, and waist to hip ratio will be measured. On the day of surgery, a preoperative lung ultrasound examination will be carried out immediately before the patient is admitted to the operating room and the lung aeration score will be calculated as described in [12]. After induction of general anesthesia, patients will be assigned to a group by opening a sealed envelope containing the allocation. All patients will be ventilated in a volume-controlled mode (VCV) with constant inspiratory flow at a tidal volume of 7 ml per kg predicted body weight (PBW), with an I:E ratio of 1:2 and an inspiratory pause of 30%. PBW will be calculated using the NIH-NHLBI ARDS Network formula. ♂: PBW (kg) = 50 + 0.91 (height (cm) − 152.4) and ♀: PBW (kg) = 45.5 + 0.91 (height (cm) − 152.4) [19].

In the intervention group, PEEP will be adjusted to a value of BMI/3 mbar for the duration of general anesthesia. In the control group, PEEP will be set at a fixed value of 5 mbar for the duration of general anesthesia. Sustained-inflation recruitment maneuvers will be performed after disconnection of ventilator circuit and in case of a drop in oxygen saturation below 90% despite ventilation with more than 60% of oxygen, with an airway pressure of 20 mbar above PEEP for 10 s in the intervention group and with an airway pressure of 30 mbar for 10 s in the control group. The lung ultrasound data will be stored anonymously and evaluation of the ultrasound images for calculation of lung aeration score will take place without knowledge of the group allocation (Fig. 1).

**Fig. 1 Fig1:**
[figure not shown]
SPIRIT figure: Schedule of enrolment, allocation, interventions, and assessments

### Criteria for discontinuing or modifying allocated interventions {11b}

If instances of hypotension or hemodynamic instability necessitating intervention occur, or if the patient experiences acute cardiac or pulmonary decompensation, the intervention will be discontinued. Treating physicians (who are not part of study team) can suspend the study at any time. The reason will be documented in the case report form. Furthermore, participants may withdraw from the study without citing a reason at any time. There is no provision for modifying the assigned intervention.

### Strategies to improve adherence to interventions {11c}

Adherence to the study protocol is ensured by continuous monitoring of the patient throughout the intervention by a member of the research team. This investigator will not only perform the pre- and postoperative sonographic examinations but will also ensure that the intervention is intraoperatively performed correctly by the clinician.

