### Concealment mechanism {16b}

To ensure that allocation is unbiased and concealed from patients and investigators, a numbered opaque envelope containing the group assignment is opened after induction of anesthesia by a data collecting member of the research team.

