## Assignment of interventions: blinding

### Who will be blinded {17a}

Trial participants will remain blinded to their randomized group assignment. However, due to the nature of the intervention, blinding is not feasible for clinicians performing the intervention, data collectors overseeing its implementation, and data analysts analyzing ventilator data, as readouts of respiratory and hemodynamic parameters inherently contain the implemented PEEP. Consequently, hemodynamic and respiratory data will be analyzed by non-blinded members of the research team. Given that this data is recorded on an ordinal scale, it is neither subject to interpretation nor distortion. The investigators evaluating the lung ultrasound data, on the other hand, will be blinded to the patient’s group allocation.

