Lung ultrasound has found widespread integration in clinical routine regarding the assessment of lung aeration in patients with dyspnea and acute respiratory failure [14] and is an established and readily available noninvasive method tool for the detection of postoperative pulmonary complications. Lung ultrasound allows early detection of changes in lung structure that are typical of PPCs, such as an increase in lung density due to atelectasis or effusions [15]. However, visualization of a single examination cannot be considered specific enough for diagnosis, thus it is deemed useful to perform an initial examination preoperatively before intubation and a follow-up examination postoperatively after termination of mechanical ventilation [12]. To establish longitudinal comparability and classify the severity of lung structural change, a standardized lung ultrasound scoring system should be applied [16]. The lung aeration score, based on the BLUE protocol [14], represents a validated score that has been successfully applied several times. Sonography is performed on spontaneously breathing patients in six regions per hemithorax, 0 to 3 points are assigned to each region according to the observed lung ultrasound pattern, and a sum is calculated. To evaluate the immediate postoperative outcome, oxygen saturation, required oxygen insufflation, and duration of stay in the recovery room will be analyzed as secondary outcome parameters. The length of stay in the recovery room will usually be half of the operating time and can be terminated as soon as the patient is hemodynamically and respiratory stable without further interventions.

To ensure reliable data collection and analysis, the team collecting the data was trained in the performance of lung ultrasound and the analysis team was trained in the use of the lung ultrasound score before the start of the study, using 20 sample patients. Therefore, to reduce examiner bias and prevent potential sources of error, acquisition and assessment of ultrasound images will always be performed by at least two different researchers. Lung ultrasound analyzers are blinded to group assignment and other clinical data.

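### The investigator who supervises the allocated PEEP also acquires the postoperative lung ultrasound, so blinded reading protects the scoring of the lung aeration score but not the images it is scored from

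*Protocol article*

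**What the plan says.** **Who scans.** Item 11c (Strategies to improve adherence) provides for "continuous monitoring of the patient throughout the intervention by a member of the research team". Of that person it says: "This investigator will not only perform the pre- and postoperative sonographic examinations but will also ensure that the intervention is intraoperatively performed correctly". The Discussion agrees, reporting that "the team collecting the data was trained in the performance of lung ultrasound".

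**Who knows the arm.** Under item 16b the allocation envelope "is opened after induction of anesthesia by a data collecting member of the research team". Item 17a states that "blinding is not feasible for clinicians performing the intervention, data collectors overseeing its implementation".

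**Who is blinded.** Item 17a continues: "The investigators evaluating the lung ultrasound data, on the other hand, will be blinded". Items 11a, 17b and 18a likewise confine ultrasound blinding to evaluation, and 18a provides two trained readers. As its measure against examiner bias, the Discussion says that "acquisition and assessment of ultrasound images will always be performed by at least two different researchers".

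**When the scans are taken.** Under items 11a and 13 the preoperative scan is done just before the patient enters the operating room, and the envelope is opened after induction. The postoperative scan follows in the recovery room.

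**What the scans feed.** Item 12 lists the change in lung aeration score as a secondary endpoint. The Discussion includes prevention of aeration loss, as assessed by lung ultrasound, among the questions the study aims to answer.

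**The concern.** A blinded reader can grade only the images supplied. If the person acquiring them knows the arm, that knowledge can affect how the examination is carried out before any blinded step begins. The Discussion offers the split between acquirer and reader as the control on examiner bias, but that split acts only on the second step.

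At stake is the credibility of one secondary endpoint. It deserves attention because it is the outcome attached to the stated aim on lung aeration, and because the Discussion says that postoperative pulmonary complications could not be evaluated in a trial of this size. A difference in aeration change between arms would be open to the objection that the postoperative images were taken by someone who had just supervised the allocated PEEP.

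**Working it through.** The point turns on who knows what and when, so the check sets the sections side by side. The plan gives no figure of its own to reproduce.

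1. **Does the operator know the arm?** Item 11c makes the operator responsible for seeing that the intervention is correctly applied. The arms differ in PEEP (BMI/3 mbar or 5 mbar, item 11a), so this cannot be checked without knowing which applies. Items 16b and 17a agree: a data collector opens the envelope, and data collectors overseeing the intervention are unblinded. Answer: yes, by design.

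2. **Does any section provide a different or blinded operator for the postoperative scan?** Items 11a, 17a, 17b, 18a and the Discussion all concern evaluation or scoring. Item 17b encourages the data collection team to preserve blinding where it can, but item 17a has already said that those overseeing the intervention cannot be blinded. Item 17a also defends unblinded handling, but only for hemodynamic and respiratory readouts. Answer: no.

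3. **Which scan is exposed?**

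| Step | Arm known to operator? | Reader blinded? |
|---|---|---|
| Preoperative acquisition | No, envelope unopened | Yes |
| Envelope opened after induction | – | – |
| Postoperative acquisition | Yes | Yes |

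4. **How does a distortion reach the endpoint?** Let b_I and b_C be the mean effects of the operator's knowledge on the postoperative score in the intervention and control arms. The preoperative scan carries no such effect. Then

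 observed difference in change = (post_I + b_I − pre_I) − (post_C + b_C − pre_C) = true difference + (b_I − b_C).

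 The baseline scan cancels none of it. The same contrast is the group-by-time term of the two-way ANOVA in item 20a, so the planned analysis does not remove it either. If the operator's knowledge has no effect, or the same effect in both arms, the bias is zero.

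5. **Can its size be obtained?** The Discussion describes six regions per hemithorax scored 0 to 3: 12 regions, so a range of 0 to 12 × 3 = 36. A shift of one grade in one region, in every patient of one arm, would move that arm's mean by 1 point. The documents give neither the SD of the change score nor any information on whether, or how far, knowledge of the arm shifts a region's grade. A false-positive rate calculated here would therefore rest on assumptions alone, and none is given.

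**The case against.** **Scoring is well protected.** Two trained readers work without knowledge of allocation, scanning is restricted to trained investigators with one named probe, and a standardized regional score is used. This stands, and it confines the gap to acquisition.

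**The article does not hide the arrangement.** A careful reader can work out from items 11c and 17a that the operator is unblinded. That is so, but item 17a does not name the operator when it sets out ultrasound blinding, and the Discussion presents the split as the control on bias.

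**Acquisition rules may be in the full protocol.** The article says nothing about image selection, clip length or repeat images. Such detail is commonly left to the full document, so its absence is not held against the plan. Such rules might limit the operator's discretion, but they would not change who holds the probe, which item 11c fixes.

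**One operator for both scans has a merit.** It keeps inter-operator variability out of a paired change. This stands and is counted as a cost of the fix.

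**The stakes are limited.** This is one of eleven listed secondary endpoints, in a trial that item 21a calls a pilot. Driving pressure is unaffected. This also stands.

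A reader might go further and infer that the ultrasound result will be biased, that its false-positive rate is inflated by a known amount, or that the article already claims the intervention prevents aeration loss. The documents support none of these. They show an opportunity for bias and no evidence of actual distortion, they give no inputs for its size, and the Discussion states an aim.

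**Conclusion.** The concern holds as a risk of bias in the acquisition of the postoperative scan, and through it in the change in lung aeration score. That the operator knows the arm is explicit in item 11c and is corroborated by items 16b and 17a. No section provides a blinded operator, and the separation of acquirer from reader does not fill the gap.

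The size is unknown: the bias equals b_I − b_C, which the documents do not allow anyone to estimate. The conclusion assumes only that lung ultrasound images depend to some degree on how the operator obtains them. It does not extend to the scoring step, the preoperative scan or the primary endpoint. The point is a worthwhile low-cost improvement and does not threaten the trial's main result.

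**What to change.** **Preferred, in item 11c:** where the existing roster allows, have the postoperative scan performed by another already trained team member who was not in the operating room and is not told the PEEP. Item 18a refers to trained members in the plural but gives neither their number nor their availability, hence the condition.

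**Otherwise:** keep the same operator under a fixed acquisition rule. Use the same 12 preset probe positions as at the preoperative scan and a fixed clip length, store the first technically adequate clip, allow no deletions, and pass all clips to the blinded readers. This needs no extra staff.

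**In either case:** record for each postoperative scan whether the operator knew the allocation, and reword item 17a and the Discussion so that blinding is claimed for reading only. The rewording remains possible after scanning is complete, but on its own it discloses the risk without reducing it.

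**Cost:** changes to protocol and working-instruction wording, and less scheduling flexibility. A change of operator adds some inter-operator variability between the two scans of a patient. The fixed rule may leave a few regions ungradable.
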